## **Objectives**

To further this aim we will

- 1) first calculate the currently observed age and sex and diabetes type specific rates of first referable retinopathy in the screening programme and describe these by calendar year
- 2) Build a predictive model and validate its prediction performance of time to first referable disease
- 3) Extend that model to utilise a hidden markov model derived measure of risk and assess whether this improves predictive performance
- 4) compare the estimated number of screenings required to maintain interval disease rate below a given threshold using the maximally predictive model from this process with a much simpler decision algorithm such as the current programme and a programme that would screen all type 1s annually and all types 2s biannually.

The models will be developed for type 1 and type 2 separately

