### Performance evaluation

The performance of the final model will then be reported from the test dataset.

Discrimination will be assessed using a C-statistic (area under the receiver operating characteristic [AUROC]). We will calculate the AUROC within age and sex strata and then take a weighted average of these to define the final AUROC.

Calibration will be summarized using a calibration plot, calibration slope, and Hosmer-Lemeshow test.

We will also report out the net reclassification indices and the IDI. However note that we consider the AUROC to be the most valid of these. Integrated Discrimination Index (IDI). The IDI =  $(IS_{new} - IS_{old}) - (IP_{new} - IP_{old})$  where IS is the integral of the sensitivity across all possible cut-off values for the new ( $IS_{new}$ ) and old models ( $IS_{old}$ ) and IP the corresponding integral of 1-specificity with the new model reflecting the model with added clinical covariates and the old model being based only on the DRS screening data. These metrics will allow us to assess how well these models improve prediction of risk for transition to referable eye disease.

In the test set we will compare the predictive performance of the prediction model with this hidden markov derived measure with the simpler indices of past screening results as described under a. above

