### Utility assessment

To be expanded: We will compare the estimated number of screenings required to maintain interval disease rate below a given threshold using the maximally predictive model from the above process with a much simpler decision algorithm such as i) the current annual screening for all programme and ii) a programme that would screen all type 1s annually and all types 2s biannually.

Since there are many ways in which policy formulations might utilise prediction risk. We will produce some examples; for instance we can show what the impact on number of screens per annum based on individualised screening intervals set by a series of thresholds of risk (e.g. 1% or 2.5% or 3%). We can also calculate the number of people who will potentially have a delay of >3 months in detection of referable disease and calculate the median 'delay' for each scenario (i.e. the interval between when they would have been screened based on current screening scheme and when they would be screened under the new scheme). The aim is that the models will be able to evaluate a wide range of potential screening policies to provide interactive feedback to policy makers.

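### The SAP does not define the 'maximally predictive' model that it carries into Objective 4, and none of the measures it gives for improvement between models is a proper score

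*SAP*

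**What the plan says.** Under Model construction the SAP plans several rival models: Poisson regression with the last screening result, Poisson regression with a weighted screening history, a hidden Markov risk score entered into the fuller model, separate models by number of previous examinations, and kernel-based methods.

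One of them goes forward. Objectives, item 4, counts screens "using the maximally predictive model from this process", and Utility assessment repeats this: "using the maximally predictive model from the above process". Neither section says how that model is identified. Among its examples, Utility assessment gives "individualised screening intervals set by a series of thresholds of risk", with 1%, 2.5% and 3% as possible values.

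On measures, Performance evaluation says of discrimination: "We will calculate the AUROC within age and sex strata and then take a weighted average of these to define the final AUROC". It adds: "We will also report out the net reclassification indices and the IDI". The next sentence reads: "However note that we consider the AUROC to be the most valid of these". The paragraph closes: "These metrics will allow us to assess how well these models improve prediction of risk for transition to referable eye disease". Calibration is also planned: "Calibration will be summarized using a calibration plot, calibration slope, and Hosmer-Lemeshow test". The section opens by saying that the test set is used to report the final model. It sets no calibration limit and describes no recalibration. The AIC appears only under Poisson regression, for backward elimination.

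**The concern.** Objective 4 can depend on absolute risk. If an interval is set so that predicted risk reaches, say, 2.5%, a model whose risks are all too high screens too often, and one whose risks are too low screens too seldom. The criterion that picks the model should therefore respond to the level of risk as well as to the ranking.

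A proper score does this: its expected value is best when the predicted probabilities are the true ones. The log-likelihood and the Brier score have this property. The AUROC, IDI and NRI do not, and these are the measures tied to improvement between models. With *maximally predictive* undefined, an analyst could choose a better-ranking but miscalibrated model and still be within the plan. Objective 3, whether the hidden Markov score improves prediction, is judged with the same measures.

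**Working it through.** The SAP gives no event rate, risk spread or numerical result on this point, so there is no figure to reproduce. Rates and spreads below are assumptions.

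**Step 1. AUROC.** It uses ranks only. Multiplying every risk by a constant leaves it unchanged. Averaging it within age and sex strata means that wrong risk levels between strata are not registered either.

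**Step 2. IDI.** In the SAP's formula, integrated sensitivity is the mean predicted risk in people with events, and integrated (1 − specificity) is the mean in people without. If p_new = c × p_old, then IDI = (c − 1) × (IS_old − IP_old). With an assumed old discrimination slope of 0.0588 and c = 1.3, IDI = 0.3 × 0.0588 = +0.018. Pure over-prediction is scored as improvement; with c < 1 the IDI is negative.

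**Step 3. All measures together.** Simulation of 400,000 person-intervals: log-normal hazard, mean 2% per year, SD of log hazard 1.2; NRI cut-offs 1/2.5/3% (assumed); IDI and NRI taken against a screening-only model. Interval T = −ln(1 − threshold)/predicted hazard, limited to 0.5 to 3 years (assumed). Screens are per person-year at the 2.5% threshold.

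| Hazard multiplied by | AUROC | IDI | NRI | Log-loss | Screens |
|---|---|---|---|---|---|
| 0.5 | 0.801 | −0.0007 | +0.102 | 0.0866 | 0.492 |
| 1 (correct) | 0.801 | +0.0217 | +0.193 | 0.0828 | 0.697 |
| 2 | 0.801 | +0.0595 | +0.068 | 0.0886 | 1.005 |

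The AUROC does not move. The IDI is largest for the model that doubles the risk. The NRI happens to favour the correct model here, but at a mean of 4% per year it is +0.278 (halved), +0.207 (correct) and −0.032 (doubled), so there it favours the halved risks. Only the log-loss is best at the correct risk and worse on both sides.

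**Step 4. Ranking against calibration.** Assumptions: mean 2.5% per year, SD of log rate 1.2 in the simpler model; the rival adds a true predictor (SD of log rate 0.3), but its rates are 1.5 times too high.
- AUROC 0.808 for the rival v 0.801; IDI +0.03. Both favour the rival.
- Log-likelihood: the rival is about 44 per 1,000 events worse (repeat runs ranged up to 54).
- Screens: with no limit on the interval, the count is proportional to the mean predicted rate, so +50%. With intervals limited to 0.5 to 3 years, +16% to +24% across the 1%, 2.5% and 3% thresholds, compared with the same rival at correct rates.

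**Step 5. Effect of changing the criterion.** At 2% per year, calibrated model A has AUROC 0.795, log-loss 0.0835 and 0.704 screens per person-year. Model B ranks better (AUROC 0.803) but has its risks halved (log-loss 0.0865, 0.493 screens) or doubled (0.0883, 1.006 screens). True risks give 0.698 screens. AUROC picks B: 0.493/0.698 = 0.71 (−29%) or 1.006/0.698 = 1.44 (+44%). Log-loss picks A: 0.704/0.698 = 1.01 (+1%). With its risks put right, B has log-loss 0.0826 and would be the better model, which is why recalibration belongs in the fix.

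**The case against.** **The SAP does not say that models are chosen by AUROC.** A reader might infer this from the stated preference, but *of these* follows the NRI and IDI and most naturally compares the AUROC with those two. It does not rank the AUROC above calibration or set a selection rule. This stands: the gap is an undefined term, not a declared wrong criterion.

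**Two of the three measures do respond to absolute risk.** A reader might infer that none penalises wrong risk, or that a miscalibrated model wins on all of them. Neither holds. For the rival in Step 4 the NRI is −0.06, against +0.03 when calibrated, and at rates multiplied by 0.67 its IDI is −0.013. What stands is narrower: none is a proper score.

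**Calibration is planned.** The plot would probably show a uniform shift, although the slope alone would not. But nothing says what follows if it does.

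**A uniform shift is unlikely for most candidates.** A Poisson log-link model with an intercept, fitted by maximum likelihood, makes predicted events equal observed events in training, and the 70/30 split is random and keeps the event ratio. A check gave observed/expected of 1.000 in training and 1.04 in test with 1,443 events, within sampling error. This covers the last result, the weighted history and the hidden Markov score used as a covariate. It is less certain if another link is used, which the SAP allows. The kernel methods are the main exposure, and the SAP says only that they will be evaluated.

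**Objective 4 may not need absolute risk.** If the interval disease rate is measured on observed disease and the cut-off tuned to it, a uniform scale error cancels. The SAP does not say which is meant. The fixed thresholds are examples, in a section marked for expansion.

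**Conclusion.** The point holds in a limited form. The SAP leaves *maximally predictive* undefined, gives no proper score for comparing rival models, and gives calibration no role before a step that can use absolute risk. It does not commit to choosing by AUROC, and it does not omit calibration.

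That these measures can favour a miscalibrated model does not depend on the assumed rates; the size does. In the Step 4 example the screen count is 16% to 24% too high with intervals limited to 0.5 to 3 years. A reader might take the 50% figure as the effect, but that needs intervals with no minimum or maximum. A shift of 1.5 is itself an assumption, credible mainly for the kernel methods. This is a cheap improvement, not a flaw that invalidates the analysis.

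**What to change.** - In Objectives and Utility assessment, define *maximally predictive* as the best out-of-sample log-likelihood of the predicted event probability per row, computed by resampling patients within the 70% training part.
- In Performance evaluation, use the same score for the hidden Markov comparison (Objective 3).
- Check calibration-in-the-large and slope of the chosen model, and recalibrate within the 70% if needed before the utility step.
- Keep the AUROC as a descriptive measure, and do not use the IDI or NRI to choose between models.
- Optional: a patient-level bootstrap interval for the difference in score, keeping the simpler model when the interval includes zero.

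Other packages, such as the Brier score with the same calibration check, would also answer the point. The cost is SAP wording, one extra statistic and, if needed, a recalibration step. The downside is that the log score is less familiar to readers than the AUROC, which is still reported.

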### **Statistical methods**

#### ***Data preparation***

### *Missing covariate data*

Covariates at a given time  $t$  will be defined by the status at the most recent assessment available prior to that screening date. If the covariate is not available in a look back up to a max of two years prior to that screening date it should be declared as missing.

Covariates missing within this time horizon of patient entry date in more than 40% of participants will be excluded. Where the missingness is  $< 40\%$  multiple imputation (see statistical methods section) will be used to assign a value based on other variables observed for the patient as well as surrounding values of that particular variable.

Covariate terms will also be set up for age x covariate and sex x covariate interactions for each covariate.

“MI” R package will be used for imputation. 10 iterations with 2 chains will be used, with seed = 1986. No consideration of event status is made in the imputation.

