### a. Poisson regression

We will use Poisson regression model with backward elimination but we may use a different link function to deal with the interval censoring - In addition we will evaluate the use of non-parametric methods for interval-censored survival analysis in place of the interval regression models.

All model fitting will be done on 70% of the data (selected randomly by patient, maintaining ratio of events), and the remaining 30% will be used for internal validation. We will randomly assign the individuals in the dataset into these two partitions.

We include current age, sex, and diabetes duration as our base set of covariates in our initial model and will then use backward elimination to drop variables from the model, using a reduction in AIC of  $< 2$  units as the selection/stopping criterion.

We will initially include a simple covariate of screening status at last screening as a covariate

We will then extend this to be a weighted score of all prior screenings weighted by how recent the measure is

The model will contain an offset term for the  $\log(\text{length of interval})$ .

We will also select across age and sex interaction terms for each covariate.

To be agreed : should we include any shrinkage/ penalizing?

*Assumption about linearity of effects of covariates :*

We will use backward elimination with multivariable fractional polynomials

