### b. Two-step analysis with multi-state modelling & survival analysis:

We will use hidden Markov models to model the DRS data. The advantages to this approach are that it allows us to model the risk for transition incorporating all available data on prior screening even though individuals have variable number of examinations at differing intervals. It also allows us to model grading misclassification as it separates the 'true but unseen grade' from the 'observed grade'. We will fit separate models by diabetes type and the models will be adjusted for age, sex and diabetes duration. As it is not feasible to extend the multi-state modelling approach to a more complex model that includes many clinical covariates we will "plug in" the risk score computed from the hidden Markov model into the fuller model that includes all available clinical covariates as described above.

**One-step survival analysis:** We will evaluate an alternative approach of not using the hidden Markov model but instead fitting separate models for individuals with 0, 1, 2 or more previous examinations. This is possible as we have a large dataset so that we will have an adequate sample size to learn a predictive model within each of these strata.

**Non-parametric methods:** We shall also evaluate non-parametric methods for interval-censored survival analysis. These kernel-based methods, which make predictions based on a function that evaluates the similarity between pairs of observations, generally outperform simple regression models for prediction though the predictions are not readily explainable.

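### Missing covariates may be imputed from readings taken after the screening date, so test-set performance may be optimistic; the SAP also names no data set other than the test set for choosing between model types

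*SAP*

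**What the plan says.** **Covariates.** Under Missing covariate data, the SAP takes a covariate's value at a screening from the last assessment before that date. It looks back at most two years and otherwise declares the value missing. Covariates missing at entry in more than 40% of participants are dropped. The others are multiply imputed "based on other variables observed for the patient as well as surrounding values of that particular variable". Event status is left out of the imputation. The section belongs to data preparation and does not distinguish development from test patients.

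**Data split.** Under Poisson regression, 70% of patients, drawn at random, are used for all fitting. Of the other patients the SAP says that "the remaining 30% will be used for internal validation". Covariates are selected by backward elimination on AIC.

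**Model types.** The SAP describes a last-status covariate, a weighted score of past screenings, a plugged-in hidden Markov risk score, "fitting separate models for individuals with 0, 1, 2 or more previous examinations", and kernel-based methods.

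**Evaluation.** Under Performance evaluation: "The performance of the final model will then be reported from the test dataset". The same section closes with a contrast between the hidden Markov version and the scores of section a: "In the test set we will compare the predictive performance of the prediction model with this hidden markov derived measure with the simpler indices". Utility assessment then counts screenings "using the maximally predictive model from the above process".

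**The concern.** The Aims describe a tool that sets the next screening interval from a patient's past screening records and the covariates held in SCI-DM. A service using it on a given day has only what was recorded up to that day. The rule for observed covariates respects this limit. The rule for missing ones does not: surrounding values are, on a plain reading, those on both sides of the date. A test patient could then be scored with a reading that did not exist when the prediction was due. The measured performance would be that of a model with slightly better inputs than it will have in service, and the screening counts shown to policy makers could inherit the difference.

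The secondary question is where the best model type is identified. Comparing two models already fixed in the test set is sound. Choosing between them there, and then reporting the winner from the same patients, would add some selection optimism.

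**Working it through.** The SAP gives no sample size, event count, expected AUROC or observed missingness, so there is no stated figure to reproduce. The numbers below are illustrations under assumptions.

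**1. The two covariate rules side by side.** Take a screening with no reading in the preceding two years. The look-back rule declares the covariate missing. The imputation rule then allows a reading from, say, a year after the screening to inform the value. The first rule is prior-only and the second is not.

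**2. What a later reading adds to the covariate.** Assume a yearly autocorrelation ρ of AR(1) form. A reading three years old explains R² = ρ⁶ of the missing value. With a second reading one year later, the correlations with the missing value are a = ρ³ and b = ρ, and r = ρ⁴ between the two readings. Then R² = (a² + b² − 2abr)/(1 − r²).

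| ρ | earlier reading only | earlier and later |
|---|---|---|
| 0.6 | 5% | 38% |
| 0.7 | 12% | 52% |
| 0.8 | 26% | 68% |

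For ρ = 0.6: (0.0467 + 0.36 − 0.0336)/(1 − 0.0168) = 0.379. This shows that a later reading is informative about the covariate. It does not measure AUROC or calibration.

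**3. Effect on AUROC.** The simulation had 400,000 rows and about 4.6% events, with logit(p) = −3.6 + 0.6x + 1.0w. The covariate x had correlation ρ with both its previous and its next reading, and was missing at random in 10%, 20% or 40% of rows. It was imputed from the previous reading and w, or from these plus the next reading. The next reading was unaffected by the event. The table gives the gain in AUROC from adding the next reading.

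| ρ | missing rows | predicted mean | random draw |
|---|---|---|---|
| 0.6 | 10% | 0.0005 | 0.0006 |
| 0.6 | 20% | 0.0011 | 0.0018 |
| 0.6 | 40% | 0.0026 | 0.0053 |
| 0.8 | 10% | 0.0004 | 0.0008 |
| 0.8 | 20% | 0.0010 | 0.0020 |
| 0.8 | 40% | 0.0022 | 0.0046 |

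For example, 0.7728 − 0.7675 = 0.0053. The gain comes from a different set of predictors and not from sampling error, so a larger database does not reduce it. If the next reading shifts by 0.25 to 0.5 SD in patients with an event, the gain is 0.0018 to 0.0149. Limits: there is one covariate, the earlier reading is only one visit old, every row (event rows included) has a later reading, and calibration was not simulated.

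**4. Choosing the best of K models in the test set.** For equally good models, optimism ≈ E[max of K standard normals] × SE(AUROC) × √(1 − r), where r is the correlation between their AUROC estimates. Assume AUROC 0.80, events in 5% of rows, K = 2 to 6 (E[max] 0.562 to 1.267) and r = 0.5 to 0.95. The Hanley–McNeil SE gives:

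| test-set events (assumed) | SE | optimism |
|---|---|---|
| 100 | 0.0269 | 0.0034 to 0.0241 |
| 1,000 | 0.0085 | 0.0011 to 0.0076 |
| 10,000 | 0.0027 | 0.0003 to 0.0024 |

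For K = 6, r = 0.5 and 1,000 events: 1.267 × 0.0085 × 0.707 = 0.0076. Unlike the effect in step 3, this one fades as events accumulate.

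**The case against.** **Imputation.** Only rows with an empty two-year look-back are affected, and later readings are one source beside the patient's other variables. That stands and limits the size. The 40% limit applies to participants at entry; a reader might take it as a share of rows, but the SAP gives no row-level figure.

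A reader might also infer that values recorded after the event, or after the care that followed it, leak into the predictors. The SAP does not support that: follow-up ends at the first event and the rows run only from entry to exit. The larger simulated range, which needs such a shift, is therefore not the one to rely on. Look-ahead does not depend on post-event records, because a reading taken after the screening that opens a row and before the one that detects disease is already too late for the prediction. If imputation used only row-level values up to exit, however, a patient's last row would have no later row to borrow from, and the simulated range would not carry over directly. The SAP does not say which source is used.

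For HbA1c, which is lagged by at least a year, borrowing the next row's lagged mean would involve little or no look-ahead at roughly annual screening. Excluding event status from the imputation prevents direct use of the outcome but does not restrict the dates of the readings used.

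**Test set.** A reader might infer that the 30% decides which model wins. The SAP never says so. Fitting and elimination are confined to the 70%, the wording on the final model can mean one already fixed, and the test-set contrast answers Objective 3 legitimately. No test-set comparison of the stratified or kernel models is described, and the utility section is marked as still to be expanded. What remains is a gap: no rule or other data set is named for choosing between model types.

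**Conclusion.** The imputation point holds. As worded, the rule lets readings from after the screening date into test-set predictors, against the SAP's own prior-only definition and the purpose of the tool. Reported AUROC, calibration and utility figures that use imputed rows may be optimistic. The size is unknown from the SAP; about 0.0004 to 0.005 AUROC is an illustration that assumes 10% to 40% of rows missing, correlation 0.6 to 0.8 between visits, and later values that are available for every row but carry no trace of the event.

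The test-set point is secondary. It is an omission to close, with probably little effect in a national database (at most about 0.002 AUROC at an assumed 10,000 test-set events).

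A reader might go further and conclude that the reported performance is unattainable in use or that the tool cannot be deployed. Neither is shown: the model can still be applied, and only imputed rows are affected.

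**What to change.** **Missing covariate data.** Replace the reference to surrounding values with a rule such as: *A missing value at a screening date is imputed only from information recorded on or before that date. Test-set rows are imputed with the model estimated in the 70% development set.*

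**Performance evaluation and Utility assessment.** State that the choice between model types is made within the 70%, for example by patient-level cross-validation, separately for type 1 and type 2 diabetes. State also that the chosen model is locked before the 30% is used, and that the 30% then serves for reporting and for one pre-named contrast, hidden Markov versus weighted score.

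**Cost.** SAP wording, some computing time, slightly less precise imputations, and possibly slightly less favourable reported performance.
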